### Intervention

5.2

Intervention group (n = 100): Administration of nebulized fentanyl (25 μg in 5 mL of normal saline) over 15 minutes, thrice daily using the traditional nebulizer. Treatment duration – 48 hours.

### Control group

5.3

Administration of nebulized 0.9% saline solution (5 mL of normal saline), over 15 minutes, thrice daily using the traditional nebulizer. Treatment duration – 48 hours

Balancing measures: If nebulization does not provide symptomatic relief in these patients, oral antihistamines will be offered to inpatients, and dexmedetomidine will be considered for ICU patients. The assigned nurse will administer all medications.

### Data management

5.4

The data gathered for this study will be uploaded to a secure database administered by the Hamad Medical Corporation IT staff (e.g., PACS). The sponsor will be the exclusive owner of the data. Source documentation will be made accessible to assist the electronic medical record. Clinical data will be recorded in each patient's source documents (i.e., the patient's medical record) by research employees. Adequate and accurate records will be kept in order to thoroughly document the research's conduct and to allow for later verification of the study results. After the research is completed, the investigators will keep all source documents, study-related papers, and data kept in the database dedicated to data collecting. As people are recruited in the experiment, data will be recorded.

### Statistical methods

5.5

A well-structured case report form will be prepared and created to collect the essential data in line with the research study design and goals. Lead research investigators will conduct and maintain data quality in terms of completeness, verification, correctness, security, and confidentiality of data. Participants will be reassured that no personal identification will be used in scientific presentations or publications, that the anonymity and confidentiality of the study results will be maintained, and that their data will be kept confidential and accessible only to the study research investigators and authorized personnel from the research ethics committee.

The chi-square^[2]^ test and the Fisher exact test will be used to evaluate categorical data, if appropriate. The unpaired ‘*t*’ or Mann–Whitney *U* test will be used to compare continuous variables (quantitative data) between the 2 independent groups. The findings will be displayed together with the relevant 95% confidence interval. In addition, if necessary, other relevant regression models will be employed to examine and quantify the impact of various variables on primary and secondary outcome measures. Using appropriate statistical graphs, pictorial presentations of the relevant data will be created. All *P* values reported will be two-tailed, with *P* values less than .05 deemed statistically significant. All statistical analyses will be performed using the statistical software program SPSS 25 (SPSS Inc., Chicago, IL).

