##### Breathlessness

4.4.1.1

The severity of breathlessness will be measured by the 10-point Borg scale [time frame: 15-minutes posttreatment]. Patients will be instructed to use this scale to rate their breathing difficulty. The scale is ranged from 0 to 10, where 10 is the maximum breathing difficulty.^[16]^

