##### Throat pain

4.4.1.2

Throat pain will be graded by the Numerical Rating Scale, in which patients will be asked to circle the number between 0 and 10 that fits best to their pain intensity. Zero usually represents “no pain at all”, whereas the upper limit represents “the worst pain ever possible”.^[17]^

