##### Cough

4.4.1.3

The cough severity score represents a simple instrument, using a 10-point scale, where the patient can indicate the severity of their cough between the 2 extremes: 1 for no cough while 100 mm is the most severe cough.^[18]^

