### Type and classification of study – randomized control trial

5.1

Baseline matching: Demographic variables and comorbidities will be compared between both groups. The severity of the disease will be compared using sequential organ failure assessment scores.

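### The stated test for continuous outcomes is unadjusted and no pre-dose symptom score is named; a pre-specified ANCOVA would gain precision and remove chance baseline imbalance from the estimate

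*Protocol article*

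**What the plan says.** All references are to the protocol article.

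- **Test.** Statistical methods (5.5) says that the unpaired t or Mann–Whitney U "test will be used to compare continuous variables (quantitative data) between the 2 independent groups". No covariate is attached to this comparison.
- **Regression.** The same section adds that "if necessary, other relevant regression models will be employed to examine and quantify the impact of various variables on primary and secondary outcome measures". The variables are not named.
- **Breathlessness.** The Borg rating has one stated time: "time frame: 15-minutes posttreatment".
- **Throat pain and cough.** Each is defined by its scale ("Throat pain will be graded by the Numerical Rating Scale"; "The cough severity score represents a simple instrument, using a 10-point scale"), with no rating time and no mention of a rating before treatment.
- **Baseline.** Section 5.1 says that "Demographic variables and comorbidities will be compared between both groups" and that "The severity of the disease will be compared using sequential organ failure assessment scores". The three symptom scores are not in that list.

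No section mentions a pre-dose symptom score, a change from baseline or a baseline-adjusted primary analysis.

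**The concern.** The primary efficacy outcomes are patient-rated symptom scores, and the objectives are worded as improvement and relief. A patient's rating after treatment can be expected to carry some of the rating before it. That link is most plausible for Borg, which is timed 15 minutes after treatment. Entry depends on tachypnea and not on any minimum dyspnea, cough or throat-pain score, so patients may start far apart on these scales.

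An unadjusted comparison of post-treatment scores leaves that spread in the error term, and the confidence interval is wider than the same 200 patients could give. If one arm happens to start worse, part of that difference stays in the estimated effect. SOFA measures organ failure, so comparing or adjusting for it is no substitute for the pre-dose score of the symptom itself. The reserve regression names no covariate and no condition for its use, so the article does not settle in advance which analysis of a primary outcome counts.

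The timing matters because an analysis plan can add a model later, but it cannot adjust for a rating that was never taken.

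**Working it through.** **Inputs from the article.** Total 200 patients (Sample size & recruitment). The intervention arm has 100 (Intervention), which leaves 200 − 100 = 100 controls. Two-sided test at 0.05 (Statistical methods).

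**Input not in the article.** The correlation r between pre-dose and post-treatment score. It is assumed, and shown at 0.3, 0.5 and 0.7.

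**The plan's own figure.** The total of 200 cannot be reproduced, because the article gives no effect size, SD, power or dropout with it. What follows is what 100 per arm can deliver, in SD units of the post-treatment score, by the normal approximation.

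**Step 1, unadjusted test.** Standard error of the difference = √(2/100) = 0.141 SD. Detectable difference at 80% power = (1.960 + 0.842) × 0.141 = 0.396 SD. At 90% power it is 0.458 SD.

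**Step 2, ANCOVA on the pre-dose score.** The variance is multiplied by 1 − r². Equivalent number per arm = 100/(1 − r²). Detectable difference = 0.396 × √(1 − r²). Power for a true effect d = Φ(d / [0.141 × √(1 − r²)] − 1.96).

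| | Unadjusted | r = 0.3 | r = 0.5 | r = 0.7 |
|---|---|---|---|---|
| 1 − r² | 1 | 0.91 | 0.75 | 0.51 |
| Variance saved | – | 9% | 25% | 49% |
| Equivalent n per arm | 100 | 110 | 133 | 196 |
| Detectable at 80% power (SD) | 0.396 | 0.378 | 0.343 | 0.283 |
| Power if the true effect is 0.4 SD | 80.7% | 84.3% | 90.4% | 97.7% |
| Power if the true effect is 0.3 SD | 56.4% | 60.4% | 68.8% | 84.4% |

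The true effects of 0.3 and 0.4 SD are illustrations and do not come from the article.

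**Step 3, chance imbalance.** The baseline mean difference between arms has SD √(2/100) = 0.141 SD, so its 95% range is about ±0.28 SD. The chance that it exceeds 0.2 SD in either direction is 2 × [1 − Φ(0.2/0.141)] = 16%. An imbalance of 0.2 SD shifts the unadjusted estimate by r × 0.2 = 0.06, 0.10 and 0.14 SD for r = 0.3, 0.5 and 0.7. Given that imbalance and no true effect, the estimate has mean r × 0.2 and SD 0.141 × √(1 − r²). It is still judged against ±1.96 × 0.141 = ±0.277 SD. The conditional type I error is then 6.0%, 7.5% and 8.7%. Averaged over all randomizations it remains 5%.

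**Step 4, would a change score do instead?** Its variance factor is 2 − 2r: 1.4 at r = 0.3, 1.0 at r = 0.5 and 0.6 at r = 0.7. Power for 0.4 SD is 66.7%, 80.7% and 95.5%. It is worse than the post-treatment score alone below r = 0.5, and below ANCOVA at all three values.

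**The case against.** The strongest reply is that a condensed article is being read too hard. The sentence on tests is generic and covers all continuous variables, including length of stay. It does not say that post-treatment values are compared alone, and an unpaired t test could be run on change scores. Section 5.1 lists what will be compared between arms, not everything that will be collected, and the case report form is not shown. A separate analysis plan could define the regression beforehand.

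Much of this stands, and it limits the point in four ways that a reader might otherwise overlook.

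- **Bias.** A reader might infer that the planned test is biased or invalid. It is not: the 6.0% to 8.7% in the working is conditional on one particular imbalance, and the unconditional level is 5%.
- **Data collection.** A reader might infer that pre-dose scores will not be recorded, or that only post-treatment values will be compared. The article does not say so; it only names no such score.
- **Confidence interval.** A reader might infer that Mann–Whitney conflicts with a promised interval for a mean difference. The article promises only a relevant 95% interval, and a Hodges–Lehmann interval can accompany Mann–Whitney.
- **Timing.** A reader might take all three outcomes to be rated shortly after a nebulization. That is stated for Borg only. Throat pain and cough could be rated later in the 48 hours of treatment, where r may be lower.

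The reply does not remove the point itself. The article does choose a test, a Borg time point and a baseline list, and all three leave out the pre-dose symptom score. The reserve regression is optional and names no covariate.

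**Conclusion.** The point holds as an improvement in precision and in protection against chance imbalance, not as an error that invalidates the trial. The stated test is unadjusted, and a better one is available for the same patients.

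The size depends on r, which no document gives. The gain is modest at r = 0.3 (9% of the variance, 0.40 to 0.38 SD detectable) and large at r = 0.7 (49%, 0.40 to 0.28 SD), with r = 0.5 between them (25%, 0.34 SD). One value of r need not fit all three outcomes. The figures also assume equal SDs and the same linear relation in both arms. Because the article states no target effect or power, no shortfall against a target can be claimed.

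The change should be made before enrolment, since the pre-dose ratings cannot be recovered afterwards.

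**What to change.** 1. In Outcomes measures, state that Borg, throat pain and cough are rated immediately before the first nebulization, and add these scores to the baseline description in section 5.1.
2. In Statistical methods, make the primary analysis of each symptom score an ANCOVA of the post-treatment score on arm and that outcome's pre-dose score. Report the adjusted mean difference with its 95% CI. Baseline SOFA may be added as a second covariate; no gain from it has been quantified here.
3. Keep Mann–Whitney as a sensitivity analysis, and do not replace the ANCOVA with a plain change score.
4. For the primary outcomes, delete the condition in "if necessary, other relevant regression models will be employed to examine and quantify the impact of various variables", so that adjustment is fixed before the data are seen.

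The cost is three short ratings per patient and a few lines of text. SOFA is already planned and the named software, SPSS, fits the model. The sample size and treatment are unchanged.

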## Objectives

2

Primary objectives: To assess the efficacy and safety of nebulized fentanyl to suppress cough, respiratory drive, improve breathlessness, and relieve throat pain in patients with COVID-19.

Secondary objectives: Overall patient outcomes (intensive care unit [ICU] or hospital stay and mortality).

Hypothesis: Nebulized fentanyl is effective and safe in providing symptomatic relief of cough, improving breathlessness, and relieving throat pain in patients with COVID-19, which is superior to saline nebulization.

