##### Drug safety

4.4.1.4

Evaluate the safety of using the nebulized fentanyl with any potential adverse events.

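### Three unranked primary efficacy outcomes share one unadjusted .05 threshold and no success rule, so the error of the superiority claim depends on a reading the protocol does not fix

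*Protocol article*

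**What the plan says.** Section 2 of the protocol article gives one primary objective covering several symptoms and safety: "Primary objectives: To assess the efficacy and safety of nebulized fentanyl to suppress cough, respiratory drive, improve breathlessness, and relieve throat pain". The hypothesis in the same section is that "Nebulized fentanyl is effective and safe in providing symptomatic relief of cough, improving breathlessness, and relieving throat pain in patients with COVID-19", and that this is superior to saline.

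Section 4.4.1 turns this into outcomes at one level:

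- 4.4.1.1: "The severity of breathlessness will be measured by the 10-point Borg scale"
- 4.4.1.2: "Throat pain will be graded by the Numerical Rating Scale"
- 4.4.1.3: "The cough severity score represents a simple instrument"
- 4.4.1.4: "Evaluate the safety of using the nebulized fentanyl with any potential adverse events"

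None of the three symptoms is placed above the others. Section 5.5 provides separate two-group tests for continuous variables and one threshold for all of them: P "values reported will be two-tailed", with P "values less than .05 deemed statistically significant". The article gives no testing order, division of alpha, composite, or statement of how many symptoms must succeed.

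**The concern.** This is a phase III trial with a superiority hypothesis. Each of three primary tests may be declared significant at .05, and the protocol does not say which pattern of results counts as success. Two things are at stake.

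- **Error rate.** If one significant symptom is enough, the claim has three chances to arise by luck, and its error exceeds the stated 5%.
- **Interpretation.** If throat pain is significant and breathlessness is not, the protocol gives no agreed reading. One person could call the trial positive and another negative, each relying on the same text, and the choice would be made after the data are seen.

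**Working it through.** **Inputs from the protocol article**

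- Primary efficacy outcomes: three (4.4.1.1 to 4.4.1.3). Drug safety (4.4.1.4) is left out because the count concerns false efficacy results.
- Per-test level: two-sided .05 (5.5), so the critical value is c = 1.96.
- Sample size: 200 in total (4.6), 100 on fentanyl (5.2), so 200 − 100 = 100 on saline.

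**Assumptions, not in the document**

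- One test per symptom, with test statistics jointly normal when there is no effect.
- A common correlation ρ between the three statistics, taken from 0 to 0.9.

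The plan states no family-wise error rate, so there is no figure of its own to reproduce; the .05 is a per-test threshold.

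**Reading A: any one significant symptom supports the claim**

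Independent outcomes, either direction: 1 − 0.95³ = 1 − 0.8574 = 0.1426.

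Independent outcomes, in favour of fentanyl only: 1 − 0.975³ = 1 − 0.9269 = 0.0731.

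Correlated outcomes, either direction, integrating over a shared factor u:

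P(at least one) = 1 − ∫ φ(u) [Φ((c − √ρ·u)/√(1−ρ)) − Φ((−c − √ρ·u)/√(1−ρ))]³ du

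For the fentanyl direction only, the second Φ term is dropped.

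| ρ (assumed) | Either direction | Favouring fentanyl |
|---|---|---|
| 0 | 14.3% | 7.3% |
| 0.3 | 13.6% | 6.8% |
| 0.5 | 12.5% | 6.3% |
| 0.7 | 10.9% | 5.5% |
| 0.8 | 9.8% | 4.9% |
| 0.9 | 8.4% | 4.2% |
| Single outcome, for comparison | 5.0% | 2.5% |

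**Reading B: all three must be significant**

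If at least one symptom has no effect, the claim needs a false result on that symptom, which has probability at most .05. No adjustment is needed.

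**Check of the correction**

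Holm compares the smallest P value with .05/3 = .0167, the next with .05/2 = .025 and the last with .05, stopping at the first failure. When no symptom has an effect, a false claim requires passing the first step. With independent outcomes that has probability 1 − (1 − .0167)³ = 4.92%.

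**Power cost**

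The article gives no effect size or SD, so these are illustrations only. With 100 per arm and an assumed difference of 1 point, going from .05 to .0167 lowers power from 94.2% to 87.3% at an assumed SD of 2, and from 80.7% to 66.8% at an SD of 2.5. This is the most that Holm can cost a single symptom, because its later steps are less strict.

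**The case against.** The strongest objection is that the inflation depends on a decision rule the protocol never states. The hypothesis in section 2 joins the three symptoms with an *and*. Read jointly, superiority requires all three, and the error stays at or below 5%. This stands: the inflation is conditional. It does not remove the point, because the sentence is a hypothesis and not a decision rule, and section 5.5 declares each P value significant on its own.

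A second objection is that multiplicity is commonly left to an analysis plan, that only a condensed article is shown, and that adjusted P values could also be compared with .05. This stands in part. A reader should not infer that no adjustment will be made; an unseen plan may contain one. But the point rests on what the text states: three equal primary outcomes and a single threshold for all P values. An adjustment elsewhere would have to be reconciled with that sentence.

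A third objection is that the two-sided figures are not rates of false benefit. This stands in full. A reader might take 11 to 14% as the chance of a false efficacy finding, but those figures include differences favouring saline. The rate of false benefit is about half as large and should be compared with 2.5%.

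Finally, a particular testing order would be partly preference. Section 4.4.1 lists breathlessness first and throat pain before cough, whereas the objective and the hypothesis in section 2 begin with cough. The documents do not settle a hierarchy.

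**Conclusion.** The point holds as an unresolved success rule with a conditional error inflation. Followed literally, sections 4.4.1 and 5.5 let any one of three symptoms be called significant at .05. Nothing prevents that result from supporting the superiority claim, with a family-wise error well above 5% across the correlations examined. The lower end of the range rests entirely on the assumed correlation; the 14.3% rests on independence.

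The documents do not support the stronger statement that the trial's error is 11 to 14%. The any-one reading is permitted but not prescribed, correlations above 0.7 give lower values, and an all-three rule would give no inflation. The ambiguity itself is certain, and it should be settled before any data are seen.

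**What to change.** In section 5.5, replace the blanket .05 for the three primary efficacy outcomes with a prespecified rule that holds their family-wise error at two-sided .05, and refer to it from section 4.4.1.

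- **Default:** Holm across breathlessness, throat pain and cough.
- **If the hypothesis is meant jointly:** state instead that superiority is claimed only when all three are significant at .05 in favour of fentanyl.
- **Acceptable alternative:** a fixed sequence beginning with Borg breathlessness, each step at .05, if the sponsor justifies the order before data are seen. Later symptoms could not then be claimed once an earlier one fails.

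Drug safety should stay a primary outcome outside this efficacy family, so that the rule does not demote it.

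The cost is a short text change and some power: Holm weakens each individual symptom claim somewhat, and the all-three rule weakens the overall claim. The change does not itself require extra patients.

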## Methods: monitoring

6

### Data monitoring & auditing

6.1

The clinical trial master file, as well as informed consent from patients, will be made available in accordance with the standards of the Joint Commission International, the Medical Research Center, and the Ministry of Public Health. Any side effects or adverse events that occur as a result of the experiment or are suspected to be associated to it will be reported to the hospital research committee and the Medical Research Center.

A registration report will be generated on a regular basis to track patient accrual and registration data completeness. A routine data quality report will also be prepared to evaluate missing data and discrepancies. The rate and amount of accrual, as well as the accuracy of evaluations and follow-up, will be evaluated on a regular basis during the research's duration, and possible concerns will be brought to the study team's attention for discussion and action. The study team may undertake random-template data quality and protocol compliance audits at least once per year, or more frequently if required. The Hamad Medical Corporation-Institutional Review Board, Ethics, and Data Safety Monitoring Board rules shall be followed for data safety and monitoring.

## Ethics and dissemination

7

### Research ethics approval

7.1

The study is submitted and under review by the Institutional Review Board-Medical Research Center at Hamad Medical Corporation in Qatar (MRC-01-21-798).

### Protocol amendments

7.2

None.

### Informed consent

7.3

The principal investigator will screen the patient pool, and those patients who meet the inclusion and exclusion criteria will be interviewed to discuss the experiment. The consenting procedure will begin with screening and then interviewing eligible patients to explain the study rationale, advantages, risks, and objectives, as well as their option to join or withdraw at any time without any consequences. The subject will be given time to select whether or not to participate in the study.

### Confidentiality

7.4

To guarantee security, patients’ data will be coded and stored in a secure database with a unique username and password. The computerized charts and reports of the patients will be accessible only to the approved research team.

### Access to data

7.5

Patients’ information will be moved to a secure database administered by the Hamad Medical Corporation IT staff (e.g., PACS). The sponsor will own any data generated as a result of this study.

